#### AGYW level

The testing of Aim 3 will be done by intention to treat analysis, examining the effects of intervention groups at both levels (clinic and individual) on PrEP readiness, uptake and adherence. PrEP uptake will be defined as any use of PrEP. We will consider both short-term uptake within the first 3 months after study enrollment and uptake at any point during the 9-month follow-up period. Initially, we will calculate the proportion of AGYW with any use of PrEP, overall, and within each study arm, calculating 95% confidence intervals using the binomial distribution. Given the need to consider the influence of the cluster randomization by clinic, we will use generalized estimating equations (GEE) [61] models with a logit link and an exchangeable correlation structure to estimate the effects of randomization groups on both short-term (3-month follow-up) and long-term follow-up period (9-month follow-up). Models will include both intervention groups (i.e., S&D reduction training and YWHC) as covariates. Effects of clustering by randomization clinic may be examined by adjusting the variance by the inflation factor [1 + (m-1)r], where *m* is the average clinic size and *r* is the interclass correlation estimate. If the Hausman assumption of correlation between the random and fixed effects is violated, then we may include fixed effects representing cluster identification.

Finally, we will include additional baseline covariates in the models, including sociodemographic factors and behavioral risks, should initial descriptive analyses suggest differences in the distribution of these factors across study arms. In subsequent exploratory analyses, we will examine the potential mediating and moderating roles of key behavioral, social, and structural factors hypothesized to influence PrEP uptake (e.g., social support; economic dependence), as outlined in Outcomes. To assess adherence in the past month, we will measure drug-level concentration, TFV-DF assessed through DBS samples, at 3, 6 and 9 months. The threshold for adherence will be established based on recommendations from ongoing studies and research designed to inform thresholds in women. Secondary adherence measures will include self-reported use, which will be examined as the number of days in the past 30 days when PrEP was taken. Using clinical/pharmacy data on PrEP dispensation and self-report of months in which PrEP was used, we will examine adherence (the number of months of PrEP use) and discontinuation. Initially, we will examine differences in the proportions of AGYW who are adherent at months 3, 6, and 9 in each study arm, calculating confidence intervals using a binomial distribution. Our analytic approaches will be similar to those described for uptake. We will use generalized linear mixed models to allow for multiple variance components, including clustering of clinics and repeated measures of adherence within individuals over time. We will use logit, Poisson, and linear regression approaches, as appropriate.

Analyses of secondary outcomes will use similar analytic approaches and examine hypotheses tied to intervention effects on behavioral risk endpoints (e.g., substance use) and on AGYW’s assessment of stigma (e.g., participants attending the S&D reduction trained clinics will report lower levels of stigma from clinic staff than participants who attend the non-trained clinics). Other model specifications, such as zero-inflated Poisson or negative binomial will be considered for count outcomes (e.g., the number of condomless sex acts) that have excess zero values or overdispersion.

From the AGYW outcomes, it is hypothesized that AGYW enrolled from clinics who received clinic-level S&D reduction training will have higher PrEP and SRH utilization than AGYW enrolled from clinics that did not receive training. AGYW enrolled from clinics that are randomized to receive the YWHC intervention will have higher PrEP readiness, uptake and adherence than those enrolled from clinics that are randomized to PrEP and SRH provision only. AGYW enrolled from communities in clinic catchment areas that are randomized to receive the YWHC will report less HIV-related risk at follow-up (e.g., GBV, substance use, condomless sex) than those enrolled from clinics that are randomized to PrEP and SRH provision only.

Missing data in terms of data management may occur because of nonresponse and study attrition. We will analyze differential attrition in relation to participants’ key demographic characteristics. Based on our prior research conducted in South Africa with AGYW who engage in sex risk behaviors, we estimate an average retention rate of 90% over the repeated follow-ups [19, 37, 62]. We will address missingness by including demographic covariates that will serve as proxies for dropout and by conducting a sensitivity analysis.

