#### Sample size and power

For the AGYW analyses, the total sample size and number of clusters (clinic catchment areas) were selected to ensure sufficient power to detect meaningful differences in our primary outcomes, while also balancing considerations tied to reducing possible contamination (exposure to the intervention in control clusters) and implementation feasibility with a set number of clinics in the study area. Sample size estimates for tests of two proportions in a cluster-randomized design [56] were conducted for a 2-sided test with significance level of 0.05, power of .80, and intra-cluster correlation of 0.01 (based on our team’s past research in Cape Town communities), assuming 10% attrition over the 9-month follow-up period [52, 57]. This was not adjusted for multiple comparisons. Based on these parameters and calculations, the study sample includes 12 clusters (defined as clinics and their catchment areas), with a total sample size of 900 AGYW enrolled, 75 per cluster (clinic catchment area). This sample was chosen to ensure that meaningful differences in the primary outcomes of PrEP readiness, uptake, and adherence between groups would be detectable. We are powered to detect a difference between 9 to 13% in primary outcomes. Power analyses were first conducted in PASS software [58] and were refined in Stata [59] (see PrEPARE Additional Power Calculation Information in Supplementary File 4).

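### The binomial confidence intervals planned for PrEP uptake and adherence ignore clinic clustering; at the protocol's own ICC a nominal 95% uptake interval covers about 87–90%

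*Protocol article*

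**What the plan says.** All of this is in the Protocol article.

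- **Uptake (Analysis, AGYW level).** "Initially, we will calculate the proportion of AGYW with any use of PrEP, overall, and within each study arm", and then "calculating 95% confidence intervals using the binomial distribution".
- **Adherence (same section).** The proportions adherent at months 3, 6 and 9 are to be looked at for differences, "in each study arm, calculating confidence intervals using a binomial distribution". No confidence level is given here; I take it to be 95%.
- **Effect estimates (same section).** For uptake: "Given the need to consider the influence of the cluster randomization by clinic, we will use generalized estimating equations (GEE"), with a logit link and exchangeable correlation. For adherence: "We will use generalized linear mixed models to allow for multiple variance components, including clustering of clinics", together with repeated measures within women.
- **Variance inflation (same section).** "Effects of clustering by randomization clinic may be examined by adjusting the variance by the inflation factor [1 + (m-1)r"]. This is optional, and it is not tied to the binomial intervals.
- **Planning values (Sample size and power).** An "intra-cluster correlation of 0.01", 12 clinics with 75 women each, and 10% attrition. The Randomization section puts three clinics in each of the four conditions.

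**The concern.** A binomial interval treats the roughly 200 women in a condition as independent. They come from three randomized clinics, and the protocol itself assumes that women in the same clinic resemble each other. It raises the clustering issue in the sentence that follows the uptake intervals, but applies the remedy only to the effect models. The intervals are therefore fixed by a named method that does not suit the design. This is not a detail left open for later.

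Uptake and adherence are primary outcomes (Outcomes section), and the adherence sentence places the intervals next to a look at differences between arms. An interval labelled 95% that covers less overstates how precisely each arm's rate is known. A reader who compares arms from these intervals also works with variances that are too small.

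**Working it through.** **Inputs from the protocol.** ICC 0.01; 75 women per clinic; 10% attrition, so m = 75 × 0.9 = 67.5 analysed; 3 clinics per condition, 6 per factorial margin, 12 in all; two-sided alpha 0.05; power 0.80.

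**Assumed.** Uptake of 30% for the example; the control rates in step 1; any ICC other than 0.01; the number of PrEP users per clinic in step 5. Clinics are taken as equal in size.

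**1. The plan's own figure.** Design effect DE = 1 + (67.5 − 1) × 0.01 = 1.665. Each margin has 6 × 67.5 = 405 women, so the effective n is 405 / 1.665 = 243. Solving the two-proportion power formula for the difference gives:

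| Control rate (assumed) | Detectable difference |
|---|---|
| 10% | 8.9 points |
| 20% | 11.1 points |
| 30% | 12.2 points |
| 40–50% | at most about 12.6 points |

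This matches the stated 9 to 13%, so the protocol's sample size does include this design effect. The descriptive intervals do not.

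**2. Width.** √1.665 = 1.29, and 1 / 1.29 = 0.775, so the binomial interval is about 22% too narrow. For one condition n = 3 × 67.5 = 202.5. At 30% uptake:

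- binomial: 1.96 × √(0.3 × 0.7 / 202.5) = 0.063, that is ±6.3 points;
- with the design effect: 0.063 × 1.29 = 0.081, that is ±8.1 points.

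The ±8.1 is a minimum, because it uses the normal quantile. At 50% uptake the half-width is 6.9 points (binomial), 8.9 (design effect, normal quantile), about 10.5 with t on 8 df (12 clinics minus 4 conditions) and about 19.5 with t on 2 df (the arm's three clinics alone).

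**3. Coverage at ICC 0.01.** Coverage = 2Φ(1.96 / √DE) − 1.

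- m = 67.5: 2Φ(1.519) − 1 = 87.1%.
- m = 75: DE = 1.74, coverage 86.3%.

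Beta-binomial simulation (true proportions 0.1, 0.3 and 0.5) gave about 87–90% for exact (Clopper-Pearson) intervals and 83–88% for Wald intervals. The design effect depends on clinic size and not on the number of clinics, so the overall interval is affected in the same way: with 12 clinics of 68 women, exact intervals covered 87.7–88.7%.

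**4. Sensitivity to the ICC (assumed values, m = 67.5).**

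| ICC | DE | Coverage by formula |
|---|---|---|
| 0.005 | 1.3325 | 91% |
| 0.01 (protocol) | 1.665 | 87% |
| 0.02 | 2.33 | 80% |
| 0.05 | 4.325 | 65% |

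**5. Adherence.** Dried blood spots are taken only from women who report being on PrEP (Follow-up assessments), and the denominator for the adherent proportion is not stated.

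- If all women are counted, step 3 applies unchanged.
- If only PrEP users are counted, with an assumed 20 to 30 per clinic, DE = 1.19 to 1.29. Coverage is then about 92–93% by formula and 92–96% for exact intervals in simulation.

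**6. Comparing two equal arms at ICC 0.01.**

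- Testing the difference with binomial variances: 2 × [1 − Φ(1.519)] ≈ 13% false positives instead of 5%.
- Asking only whether the two intervals fail to overlap: 2 × [1 − Φ(3.92 / √(2 × 1.665))] = 3.2%.

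**The case against.** **Inference is already protected.** Both binomial steps are introduced as initial, and the effects come from GEE or mixed models with clinic clustering. This stands, and it is the main reason why the point is minor. It does not make the intervals right: they are stated by method, and one of them by level.

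**Much lower coverage.** A reader might infer that coverage drops to about two thirds. That needs an ICC of about 0.05, five times the planning value and nowhere in the document. It is a sensitivity figure and not a consequence of the plan.

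**Same shortfall for adherence.** A reader might also carry the uptake figure over to adherence. The documents do not settle this. The intention-to-treat statement and the reference to proportions of AGYW suggest that all women are counted; the blood-spot sampling suggests users only.

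**Misleading non-overlap.** It is tempting to say that non-overlapping intervals would be mistaken for arm differences. At ICC 0.01 equal arms fail to overlap only about 3% of the time, because non-overlap is a conservative rule. The 13% arises only if someone tests a difference with binomial variances, which the protocol does not announce.

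**A condensed article.** The interval method for descriptive tables is commonly left to the analysis plan. Here, however, the article names a method, and that method does not fit the design.

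**Conclusion.** The point holds and is minor. The planned binomial intervals for uptake and adherence ignore clinic clustering. At the protocol's ICC of 0.01, with 67.5 women analysed per clinic, uptake intervals are about 22% too narrow and cover about 87% by formula, or roughly 87–90% if exact intervals are used. If the ICC were 0.02 to 0.05, which is an assumption, coverage would fall to about 80% to 65%. For adherence the shortfall ranges from almost none (92–96% coverage with an assumed 20–30 users per clinic) to the same as for uptake, depending on the denominator.

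The clustered models protect the treatment-effect estimates and tests. The error lies in the descriptive error bars, and in the invitation to look at differences in adherence between arms alongside them.

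**What to change.** In both sentences of the AGYW-level analysis section:

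1. Keep the observed proportions, overall and by arm.
2. Replace the binomial interval with a cluster-adjusted one. Use either a cluster-robust variance or the [1 + (m−1)r] inflation that the section already names, with a small-sample t quantile. State the degrees of freedom, because the choice matters (step 2 of the working).
3. State that arms are compared only through the GEE or mixed models.
4. State the denominator for the adherent proportion.

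If marginal predictions from a model are preferred for the four conditions, that model must contain the S&D-by-YWHC interaction. The uptake model as described enters the two interventions as covariates and mentions no interaction. Predictions from a model with main effects only need not match the observed proportions in the four conditions.

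The cost is a change of wording and wider intervals. No new data are needed, and the effect analyses do not change.

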#### Clinic level

AGYW service utilization will be assessed and analyzed through clinic level data at each of the 12 study clinics during an 8-month period pre- and post-training (e.g., HIV testing; number of PrEP prescriptions). Baseline and follow-up clinic staff surveys will be analyzed to examine changes in attitudes and stigma at the clinic level. Initial analyses will be descriptive and evaluate group differences comparing intervention and control clinics using unpaired t-tests with unequal variance or nonparametric tests, as appropriate. Using multilevel modeling approach, we will investigate and account for clustering at the clinic level. We will use difference-in-differences (DD) methods as done in another South African study to examine utilization of services by AGYW and staff attitudes and behaviors in the 8 months between intervention and control clinics [60]. The DD estimator reflects the average change in clinics that received S&D reduction training, after the average change in utilization in control clinics is subtracted, assuming parallel trends in clinics over time had the S&D reduction training not been implemented. DD estimates will be calculated for each outcome separately; models will include covariates for time (pre- vs. post-intervention), treatment (training vs. no training) and an interaction between the two. The clinics identified are similar in size, services, and populations served. Any clinic features for which we cannot achieve balance through the design will be included as covariates in the multivariable DD analyses. A stigma score will constitute one primary outcome for these analyses. To examine short-term changes between pre-intervention and 4-month follow-up, DD methods can be used to compare the average change in stigma scores in clinics that received S&D reduction training, removing any changes observed in control clinics. We will use generalized estimating equations (GEE) [61] to examine provider-level stigma scores measured at 4- and 8-month follow-up comparing trained and untrained clinics, accounting for clustering at the clinic-level.

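### The AGYW-level primary GEE runs on 12 clinics with no few-cluster correction named, and the clustering adjustments the article offers do not supply one

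*Protocol article*

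**What the plan says.** The Sample size and power section assumes "a 2-sided test with significance level of 0.05, power of .80, and intra-cluster correlation of 0.01" and concludes that "the study sample includes 12 clusters (defined as clinics and their catchment areas), with a total sample size of 900 AGYW enrolled, 75 per cluster". It then states: "We are powered to detect a difference between 9 to 13% in primary outcomes".

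The Randomization section describes three strata of four clinics, allocated 1:1:1:1 within each stratum. Each factor is therefore compared on 6 versus 6 clinics.

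For the primary AGYW outcomes, the AGYW level section says "we will use generalized estimating equations (GEE) [61] models with a logit link and an exchangeable correlation structure". The listed covariates are the two interventions; the strata are not listed. Baseline sociodemographic and behavioural covariates may be added if they look imbalanced. Two clustering options follow, both worded as possibilities: inflating the variance by [1 + (m-1)r], and adding clinic fixed effects if a Hausman condition fails. The article names no variance estimator and no reference distribution.

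For clinic staff, the Clinic level section plans "generalized estimating equations (GEE) [61] to examine provider-level stigma scores", again on 12 clinics.

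**The concern.** The usual GEE sandwich variance and its normal reference distribution are justified by a large number of clusters. With 12 clinics and three between-clinic parameters (intercept and two factors), two errors point the same way. The sandwich variance is too small on average, and 1.96 replaces a t value on few degrees of freedom. Omitting strata that differ in outcome pushes the other way, because the stratum differences then count as noise.

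This is the efficacy test for both interventions. If it is run in the usual form, its true error rate depends on how much the strata happen to differ, which nobody knows in advance. At one end, false positives are more than twice the nominal rate and intervals are too narrow. At the other end, the test is very conservative and loses power.

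**Working it through.** **Inputs from the article.** 12 clinics, 75 enrolled in each, 10% attrition (m = 67.5 analysed per clinic), ICC 0.01, two-sided 0.05, 80% power, 6 v 6 clinics per factor. **Assumed:** control or base rates of 10% to 50%, since the article gives none.

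**1. The stated detectable difference.** Design effect = 1 + 66.5 × 0.01 = 1.665. Effective n per factor level = 6 × 67.5 / 1.665 = 243.2. Solve d = (1.960 + 0.842) × √{[p(1-p) + q(1-q)]/243.2} with q = p + d:
- p = 10%: 2.802 × 0.0316 = 8.9 points.
- p = 40%: 2.802 × 0.0449 = 12.6 points.

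This reproduces 9 to 13, using normal critical values. The same equation on t gives:
- t(9), 2.262 + 0.883 = 3.145: 10.1 to 14.1 points.
- t(7), 2.365 + 0.896 = 3.261: 10.5 to 14.6 points.

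**2. Analytic error rate, strata alike.** With equal clinic sizes, the sandwich variance of a factor effect is close to RSS/36, where RSS is the residual sum of squares of the clinic means. The true variance is 12σ²/36. Since RSS has mean 9σ², the sandwich averages 9/12 of the truth.
- Two factors only: 2 × P(t9 > 1.96 × √(9/12)) = 2 × P(t9 > 1.697) = 12.4%.
- Strata added, 5 parameters, 7 df: 2 × P(t7 > 1.96 × √(7/12)) = 2 × P(t7 > 1.497) = 17.8%.

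**3. Why omitted strata reverse it.** At a base rate of 30%, σ² = 0.21 × 1.665/67.5 = 0.0052. Shifts of -5, 0 and +5 points add 4 × (0.05² + 0.05²) = 0.020 to an expected RSS of 9 × 0.0052 = 0.047. Shifts of ±10 add 0.080. Each factor is balanced within strata, so the effect estimate is unaffected. The ratio of expected sandwich variance to truth goes from 0.75 to about 1.07 (±5) and 2.04 (±10).

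**4. Simulation under the null.** Beta-binomial clinics, Binomial(75, 0.9) analysed, logit exchangeable GEE, ICC 0.01, base rate 30%. There were 6,000 runs without a shift and 2,500 per shift. KC = Kauermann-Carroll variance.

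| Stratum shift | Two factors, sandwich, z | Two factors, KC, t(9) | Factors + strata, sandwich, z | Factors + strata, KC, t(7) |
|---|---|---|---|---|
| none | 11.9% | 4.7% | 17.0% | 4.9% |
| ±3 points | 11.4% | 4.3% | 18.9% | 5.2% |
| ±5 points | 6.7% | 2.1% | 18.4% | 4.4% |
| ±10 points | 1.5% | 0.3% | 18.2% | 4.9% |

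Without shifts, the uncorrected two-factor test gives 11.5% to 12.5% over base rates of 10% to 50% and ICCs of 0.001 to 0.05. A standard package's default GEE gave 13.7% and 12.0% for the two factors (5,000 runs). With clinic sizes varying (CV 0.4), the uncorrected rates rise to 14.1% without strata and 20.4% with them, and KC on t(7) gives 6.1%.

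A further check used least-squares regression of clinic proportions on both factors and stratum with t(7): 40,000 runs per setting, base rates 10%, 30% and 50%, and shifts up to ±10 points where the rates allow. It rejected in 4.8% to 5.1% throughout. In the same runs, the sandwich z-test on clinic proportions with strata omitted and a ±5 shift gave 3%, 7% and 8% at base rates of 10%, 30% and 50%.

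**5. The adjustments offered.** [1 + (m-1)r] scales a variance for within-clinic correlation. It does not correct the downward bias of a variance estimated from 12 clinics, and it does not change the reference distribution. Clinic fixed effects use all 12 between-clinic degrees of freedom. Each intervention indicator is then an exact sum of clinic indicators, so neither effect can be estimated.

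**The case against.** The strongest objection is that the article is silent on the variance estimator and reference distribution. A GEE with a corrected variance and a t reference is compatible with every word of the AGYW level section, and such details usually sit in the SAP, which was not available for this check. That stands in part: it cannot be said that the trial will use an uncorrected z-test. But the article does address clustering adjustments, and the two it names do not deal with few clusters. Its detectable difference also reproduces with normal critical values. A condensed description that simply left the matter to the SAP would not be a finding.

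A reader might infer that the trial has a type I error of 12%. The documents do not support a single figure. The 12% needs the default sandwich with z and strata that do not differ. The Randomization section stratified precisely because clinics may differ in ways that bear on the outcomes. The 17-19% needs strata in the model, and the article does not list them.

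A reader might also count how often at least one of the two factors is falsely significant, which is about 22% when strata are alike. That mixes in multiplicity: two valid independent 5% tests already give 1 - 0.95² = 9.75%, and the article says openly that "This was not adjusted for multiple comparisons". The figure is not evidence for this point.

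Extending these rates to the staff stigma scores or the mixed models is not supported either. Staff numbers, scale and ICC are not given, other analyses are planned alongside that GEE, and no rate was computed. The 0.05 level is itself taken from the sample-size section; the AGYW level section states none.

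**Conclusion.** The point holds in conditional form. The AGYW-level GEE on 12 clinics names no few-cluster method, and its listed options do not provide one. Run with the usual sandwich and normal reference, it does not reliably hold 0.05: about 12% with similar strata, about 7% and 1-2% with strata omitted and shifted by ±5 and ±10 points, and 17-19% with strata added. The shifted figures assume a base rate of 30%. All of these assume near-equal clinic sizes; the 12% depends little on base rate or ICC. The same concern applies in principle to the staff stigma GEE but is not quantified.

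**What to change.** Pre-specify, before analysis, one primary method for the AGYW outcomes. Fit both factors and the three randomization strata, with a Kauermann-Carroll (or similar) corrected variance and t on 12 - 5 = 7 df. A regression of clinic proportions on both factors and stratum with t(7) is an equivalent choice. Do not settle for t(9) without strata: it is very conservative when strata differ (2.1% and 0.3% at ±5 and ±10 points). Withdraw the clinic fixed-effects option for the intervention effects. Limit any added covariates and say how the degrees of freedom change if clinic-level ones enter.

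A within-stratum permutation test is an optional check. Holding the other factor fixed, there are (2 × 2)³ = 64 allocations per factor, with a smallest two-sided p of 2/64 = 0.031. The fuller set of 6³ = 216 presumes that the other intervention has no effect.

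State a few-cluster method for the staff stigma GEE as well. Restate the detectable difference on the t basis: about 10.5 to 14.6 points on t(7) under the same inputs and assumed rates.

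The cost is SAP wording and standard software options, with no new data. Intervals become wider: if strata do not differ, by roughly 2.365/1.697 = 1.39 relative to the uncorrected two-factor GEE. If the SAP already contains such a method, confirming it is enough.

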### Randomization

Stratified randomization was conducted via SAS Software after clinic selection was finalized. The sample of 12 clinics was first grouped into three strata (peri-urban/city, peri-urban/provincial, and semi-rural/provincial) based on geographic location type (peri-urban vs. semi-rural) and clinic administration type/jurisdiction (city vs. provincial), with four clinics in each stratum. Within each stratum, clinics were then randomly assigned to study conditions based on a 1:1:1:1 allocation. Because there may be important differences pertinent to the outcomes that cannot be made homogenous, such as geographical region, stratified randomization was conducted to achieve even distribution of these factors across study arms. This reduces variability in the estimation of the intervention effect, with resulting increases in power/precision of estimates [49].

The six clinics randomized to receive the S&D reduction training will participate in workshops aimed to reduce clinic staff’s S&D attitudes and behaviors toward AGYW. For the 6 clinics randomized to the YWHC, AGYW participants recruited from communities in clinic catchment areas will be asked to participate in two workshops.

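### The named models leave out the randomisation strata (and YWHC in the clinic-level model), so the reported standard errors and tests do not show the precision gain claimed for stratification

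*Protocol article*

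**What the plan says.** The Randomization section places the 12 clinics in three strata of four, formed from location type and jurisdiction, and assigns one clinic per stratum to each of the four conditions. It gives the reason: "This reduces variability in the estimation of the intervention effect, with resulting increases in power/precision of estimates [49".

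The AGYW level section fixes the terms of the GEE: "Models will include both intervention groups (i.e., S&D reduction training and YWHC) as covariates". Further baseline covariates are to be added if descriptive analyses suggest that the arms differ on them.

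The Clinic level section fixes the DD terms: "models will include covariates for time (pre- vs. post-intervention), treatment (training vs. no training) and an interaction between the two". Other clinic features are to be added where the design could not balance them. The same section plans a GEE of staff stigma scores at 4 and 8 months, comparing trained with untrained clinics.

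No section places the strata in any model, or YWHC in the DD model.

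**The concern.** Stratified allocation removes between-stratum differences from the treatment contrast. A model without stratum terms still counts those differences as residual between-clinic variation. The standard error is then too large for the estimate it accompanies, and the gain that the Randomization section claims does not appear in the interval or the test.

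The covariate rules do not repair this. They respond to imbalance, and the strata are exactly balanced over both factors by the allocation. The same holds for YWHC in the DD model. The optional fixed effects for cluster in the AGYW level section do not help either: both interventions are assigned by clinic, so clinic fixed effects would absorb them.

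YWHC matters to the DD model because its monthly check-ins and refill reminders can act on service use and PrEP prescriptions, which are among the outcomes analysed there. At stake is precision that the design has already paid for, in a trial with few clusters.

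**Working it through.** **1. The plan's own figure.** Inputs from Sample size and power: "2-sided test with significance level of 0.05, power of .80, and intra-cluster correlation of 0.01", "assuming 10% attrition over the 9-month follow-up period", and 12 clusters "with a total sample size of 900 AGYW enrolled, 75 per cluster (clinic catchment area". Each factor compares 6 with 6 clinics.

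- Analysed per clinic: 75 × 0.9 = 67.5; per arm: 6 × 67.5 = 405.
- Design effect: 1 + (67.5 − 1) × 0.01 = 1.665; effective n per arm: 405 / 1.665 = 243.
- The article gives no control-arm proportion (it refers to a supplement not at hand: "see PrEPARE Additional Power Calculation Information in Supplementary File 4"), so 10% to 50% is assumed. The two-proportion formula gives detectable differences of 8.9 points at 10%, 12.2 at 30%, and 12.6 at 40% and 50%.

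This reproduces "We are powered to detect a difference between 9 to 13% in primary outcomes" as a main-effect comparison. No credit for stratification enters it.

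**2. True and reported standard error at participant level.** Assumptions: 30% control rate, total ICC 0.01, 68 analysed per clinic, and a share s of the between-clinic variance explained by strata (not in the article, so taken from 0 to 1).

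- Between-clinic variance: 0.01 × 0.3 × 0.7 = 0.0021. Sampling variance of a clinic proportion: 0.99 × 0.21 / 68 = 0.00306.
- The contrast of 6 with 6 clinics has variance (variance per clinic) × (1/6 + 1/6), that is, divided by 3.
- True SE: √{[(1 − s) × 0.0021 + 0.00306] / 3}.
- Reported SE without strata: the stratum sum of squares, 12 × s × 0.0021, stays in a residual with 12 − 3 = 9 df. This gives √{[(1 − s) × 0.0021 + 0.00306 + (12/9) × s × 0.0021] / 3}.

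| s | True SE | Reported SE, strata omitted |
|---|---|---|
| 0 | 0.0415 | 0.0415 |
| 0.5 | 0.0370 | 0.0428 |
| 1 | 0.0319 | 0.0442 |

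The true SE falls as the strata explain more, whether or not they are modelled. The reported one rises.

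**3. Power and type I error.** Simulated linear model on the 12 clinic proportions, 12.5-point effect, t-test with 9 df without strata (critical value 2.26) and 12 − 5 = 7 df with strata (2.36):

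| s | Power without strata | Power with strata | Type I error without strata |
|---|---|---|---|
| 0 | 74% | 71% | 5% |
| 0.5 | 74% | 80% | 2.7% |
| 1 | 73% | 89% | 0.9% |

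With strata, type I error stays at about 5%.

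**4. GEE without a small-sample correction.** With sandwich standard errors and normal critical values at ICC 0.01, type I error without strata is 11.9%, 7.7% and 4.0% for s = 0, 0.5 and 1. Adding strata without a correction moves it to 17–18%.

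**5. DD model.** Differencing removes fixed stratum levels, so only stratum differences in change matter. In clinic change scores with residual SD 1 and a training effect of 1.8 SD, omitting YWHC has this effect:

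| YWHC effect on change (SD) | Power, YWHC omitted | Type I error, YWHC omitted |
|---|---|---|
| 0 | 80% | 5.1% |
| 0.5 | 78% | 4.6% |
| 1 | 71% | 2.9% |
| 2 | 46% | 0.5% |

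With YWHC included, power is about 79% throughout.

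**The case against.** The strongest reply is that this is a condensed article, the SAP is not shown, and stratification factors are often listed only there. The covariate sentences do not say that nothing else may enter. This stands in part: nobody can conclude that the final models will lack the strata. But the article does more than stay silent. It names the terms, and it gives rules for adding others that cannot reach factors balanced by design.

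The second reply is that the size cannot be known, and this stands. A stratum spread of ±0.3 or ±0.5 logit around 30% would by itself add about 0.013 or 0.034 to the ICC. A reader who places such spreads on top of 0.01 would infer a collapse in power, but that mostly reflects total clustering well above the planned value. Hence the total is held at 0.01 here.

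Other inferences go beyond the documents:

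- That the design's precision is lost. The estimate keeps it; only its reported uncertainty does not show it.
- That the planned tests are conservative as written. This holds for a small-sample-valid test. The article names no such correction, and an uncorrected GEE on 12 clinics is anti-conservative unless strata explain most of the ICC.
- That the sample size fails. The stated detectable difference never relied on stratification.
- That omitting YWHC biases the DD estimate. In a balanced factorial without interaction it does not; it affects the standard error only. The reminder mechanism also bears on service use more than on staff attitudes.

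**Conclusion.** The point holds in a limited form. The models as named do not analyse the trial as it was randomised, and this sits badly with the protocol's own reason for stratifying. A valid test without strata is conservative whenever the strata predict the outcome. At the planned ICC, including them changes power by anything from a loss of about 3 points to a gain of about 16 (73% to 89%). The gain is about 6 points if strata explain half of the between-clinic variance. These figures rest on an assumed 30% control rate, equal clinic sizes, a 12.5-point effect and an assumed stratum share.

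At clinic level, omitting YWHC costs little unless it shifts clinic change by about 1 SD or more. Strata matter to the DD model only through differing trends. They matter more directly to the 4- and 8-month staff stigma GEE, for which no differencing is stated.

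**What to change.** - **AGYW-level models and the staff stigma GEE:** include stratum (2 df) as a fixed effect regardless of observed balance, and name a small-sample correction for 12 clusters in the same sentence. The two belong together, since strata without the correction would worsen type I error.
- **DD model:** add YWHC and YWHC-by-time. Add stratum-by-time if trends may differ between strata.

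This is a wording change in the analysis plan, to be made before outcomes are compared by arm; if the SAP already says this, cite it. It needs no new data and no change to the sample size. The cost is 2 degrees of freedom, about 3 points of power if the strata turn out not to predict the outcome. Stratum-by-time terms in the DD model cost about the same (79% to 76% in the change-score simulation without stratum trends).
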